### Intervention

A recent study demonstrated that participants with higher vitamin K1 intakes had a significant reduction in risk for CAS with subsequent aortic valve replacement, heart failure, or cardiovascular death.^32^ In that study, vitamin K1 intakes (median 191.6 µg/day) among participants were much higher than the currently recommended dosages.^35,36^ A randomized, controlled trial previously showed that a dose of 2 mg of vitamin K1 reduced the rate of progression of AVC in a cohort of patients with CAS and aortic sclerosis over a period of 12 months.^31^ In the PASSPORT trial, patients with aortic sclerosis will be excluded and only those with at least mild CAS will be included. The dose of vitamin K1 supplementation will be 10 mg because it is likely that participants in the PASSPORT trial will have advanced valvular calcification, necessitating a higher therapeutic dose of vitamin K1 to retard disease progression. Furthermore, 10 mg of vitamin K1 supplementation is safe to use in patients and a previous trial documented no adverse effects.^37^ Participants will spend a mean time period of 16 months on the PASSPORT trial.

The vitamin K1 10 mg capsules and matching placebo capsules (micro-cellulose) will be sourced from Nutrition Care Pharmaceuticals Ltd (Melbourne, Victoria, Australia). The investigational product will be packaged into bottles of 100 capsules by Nutrition Care and will be stored and dispensed by the clinical trials pharmacy of Royal Perth Hospital.

### Trial duration/schedule

The planned schedule of events for the trial is outlined in *Table 2*. After providing consent for the study, participants will attend a baseline visit. At the baseline visit, information regarding demographics, comorbidities, medications, and supplements will be collected. Dietary nutritional intake will be assessed using the Cancer Council Victoria Dietary Questionnaire for Epidemiological studies (DQES V3.2).^38^ The baseline clinical assessment will include a recording of height, weight, and blood pressure. To improve accuracy, blood pressure measurements will be taken using an automated sphygmomanometer and in the sitting position.

**Table 2 oeaf144-T2:** Schedule of events for baseline, 3-monthly follow-up, and final visits

Study event	Baseline visit	3-monthly follow-up	Final visit
Echocardiogram	X		X
CTAVC scan	X		X
Demographics	X		
Comorbidities	X		
Medications	X		
Supplements	X		
Clinical examination	X		X
Dietary intake (DQES v3.2)	X		
Blood sample	X		X
IP distributed	X	X	
IP collected		X	X
Pill count		X	X
BMAS		X	X
Randomization	X		

BMAS, Brooks Medication Adherence Scale; CTAVC, computed tomography aortic valve calcification; DQES v3.2, Dietary Questionnaire for Epidemiological Studies Version 3.2; IP, investigational product.

Baseline investigations will include a 12-lead electrocardiogram (ECG); blood tests, including serum creatinine, corrected calcium, phosphate, and cholesterol profile, and the ratio of serum undercarboxylated osteocalcin to total serum osteocalcin (ucOC/tOC), an established method of measuring vitamin K status;^39,40^ a standardized transthoracic echocardiogram according to current guidelines;^41^ and a standardized low-dose, ECG-triggered, non-contrast CT-AVC score scan, where image quality will be optimized by achieving a target heart rate <60 beats per minute, as per the local clinical protocols.^42^ Acquisition parameters for the CT-AVC will include a minimum 64-slice scanner, 120–140KV with tube current modulated according to body weight. Image reconstruction will be performed in the diastolic phase (60–80% of the RR-interval) at both 3 and 1 mm slice thickness. Radiation dose will be minimized by using prospective tube current modulation and other techniques.

Once enrolled in the trial, participants will be randomized to either vitamin K1 or placebo and given a 3-month supply of the investigational product. Participants will be given a contact number and email address for the trial coordinator and requested to report any interruptions to treatment. They will also be also advised to avoid taking vitamin K1 supplements and to inform the trial coordinators if they are prescribed warfarin. The community doctor and cardiologist for each participant will be informed in writing about recruitment to the trial and provided with contact details for the trial coordinator.

### Follow-up and trial termination

Participants will be required to present in person every 3 months for clinical review. Changes to medications and important clinical updates, such as diagnosis of new medical conditions, admission to hospital, and any potential adverse events related to the investigational product will be recorded. At each follow-up visit, participants will be supplied with investigational product for 3 months. Follow-up of participants will continue for a minimum of 12 months (mean 16 months, maximum 21 months, *Figure 1*).

At the final follow-up visit, all participants will have a repeat clinical assessment and investigations which were performed at baseline (*Table 2*).

### Adherence and withdrawal from trial

To assess adherence to the investigational product, participants will complete the Brooks Medication Adherence Scale, and pill counts will be performed at each follow-up visit. The Brooks Medication Adherence Scale will be used due to its concise, 4-question, yes/no format which will provide information on both unintentional and intentional non-adherence to the investigational product. Additionally, the change in ucOC/tOC from the baseline and final visits will be compared which will provide information on adherence to the vitamin K1 for participants in the treatment arm.

Participants may leave the study by withdrawing their consent to participate at any time and for any reason. Any data collected until the date of withdrawal will be retained and used in the final analysis.

### Study outcomes

The primary outcome of the trial is progression of AVC volume score measured by non-contrast cardiac CT.^43^ For each participant, the annualized progression of AVC volume will be calculated as (follow-up AVC minus baseline AVC) ÷ time between scans in decimal years. Secondary outcomes will include the annualized progression in AVC density and AVC Agatston;^44^ changes in standard transthoracic echocardiographic indices of CAS severity, including peak transvalvular velocity, mean pressure gradient, aortic valve area, and aortic valve dimensionless index and the change in left ventricular mass, between baseline and study end. Other outcomes will include an analysis of the safety profile of high-dose vitamin K1 intake.

All study outcomes and clinical events will be assessed by an independent committee, blinded to treatment allocation.

### Statistical considerations

The primary intention-to-treat analysis will evaluate the within-group change in CT-derived AVC volume scores between baseline and study end (mean 16 months, minimum 12 months, maximum 21 months), using a repeated-measures general linear model. The model will include fixed effects for treatment group (vitamin K1 10 mg/day vs. placebo), duration of follow-up (baseline to final visit), and their interaction (treatment × duration of follow-up), with subject as a random effect. Baseline covariates (e.g. age, sex, baseline AVC score) will be included to adjust for potential confounders. The *treatment × time* interaction will estimate and test the between-group difference in mean AVC change, assessing whether the active treatment significantly attenuates AVC progression compared to placebo. Model assumptions (normality, homogeneity of variances) will be verified using diagnostic plots and tests, with transformations applied if needed.

A prior open-label study, using CT-derived AVC volume quantification, reported a 103μL (57%) lower AVC progression in 38 subjects who received vitamin K1 (2 mg per day) for 12 months when compared with 34 control subjects.^31^ Based on this, the PASSPORT trial, which will have 54 subjects per study arm (total 108), will provide 90% power to detect a 57% difference in AVC progression (181 μL in controls vs. 78 μL for active treatment) between the groups, assuming a common standard deviation of 165 μL. This sample size will also provide 80% power to detect a 49% difference and 70% power to detect a 40% difference, at a significance level of 5%. We anticipate a low dropout rate of 5–10% based on previous experience with similar cardiovascular trials,^37^ supported by robust follow-up procedures and regular participant contact. However, in the event of a loss to follow up of up to 25% (from 54 to 41 subjects per arm), the trial would retain 80% power to detect the primary effect (57% difference in AVC progression).

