## Background and rationale

Calcific aortic valve stenosis (CAS) is the leading cause of valvular heart disease-related mortality and the third most frequent cardiovascular disease, after coronary artery disease and systemic hypertension, in high-income countries.^1^ For patients with severe and symptomatic disease, the risk of death within 2 years exceeds 50% in those who do not receive valve replacement,^2^ and the mortality rate of patients with CAS regardless of severity is higher than the general population.^3^ The prevalence of CAS increases with age, affecting 1% of patients aged 60 to 69 years and 10% of those aged 80 to 89 years.^4^ Whilst the burden of this deadly disease is increasing in tandem with the ageing population, the only effective treatment is replacement of the stenotic valve, either surgically or using a transcatheter approach, which both confer significant risk of peri- and post-procedural complications, and have a high cost.^5^ There is a clear need to develop a pharmacotherapy to prevent or reduce the progression of this valvulopathy.

The build-up of calcium on the aortic valve is the main driver of CAS. Indeed, the degree of aortic valve calcification (AVC) in patients with mild or moderate CAS is a key predictor of disease progression.^6,7^ The development of AVC is a complex, metabolically active, cell-mediated process, regulated by multiple genetic and environmental factors.^8,9^ Shear stress and other risk factors cause valvular endothelial injury and subsequent extravasation of lipids into the interstitium. These lipids are then oxidized in a process which promotes inflammation, differentiation of valvular interstitial cells into myofibroblasts and osteoblast-like cells, and calcification.^10^ The detection of these early microcalcifications using positron emission tomography scans predicts the later development of macroscopic calcifications, detectable on computed tomography (CT) scans, within 2 years.^11,12^ The progressive calcification of valvular tissue may ultimately cause transvalvular flow obstruction. Multiple trials using various pharmacotherapies to target this calcification pathway and its upstream promoters using agents, such as statins,^13–16^ renin–angiotensin–aldosterone system blockers,^17–19^ and anti-osteoporosis treatments (bisphosphonates, RANKL inhibition), have failed to show a reduction in CAS progression.^20^

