A potential limitation of this trial is confounding by dietary vitamin K1 intake and baseline vitamin K1 status, which may vary between participants and might obscure the effect of vitamin K1 supplementation. To address this, baseline and final blood tests will measure the ucOC/tOC, a validated biomarker of vitamin K1 status. Each participant will also have a baseline dietary nutritional intake assessment, using the DQES V3.2 questionnaire,^38^ which has been developed and validated for assessing food and nutrient intakes in Australia.^45,46^ Although the DQES V3.2 does not directly quantify vitamin K1 intake, estimated intake will be derived from key foods using published nutrient databases. Baseline ucOC/tOC and estimated dietary vitamin K1 intake will be included as covariates in the repeated measures general linear model alongside other baseline covariates to adjust for potential confounding. Exploratory sensitivity analyses will assess treatment effect heterogeneity by baseline vitamin K1 status to evaluate if dietary or baseline status attenuates the effect of supplementation. Another potential limitation of the trial is the use of non-contrast CT. CT AVC quantification correlates well with CAS disease severity in most patients,^47^ but this modality does have some limitations. Approximately a quarter of individuals with severe CAS, particularly among females, younger patients, and those with a bicuspid valve, have lower levels of valvular calcification because in these cohorts the disease is predominantly driven by fibrotic change.^7,48^ However, CT demonstrates excellent scan-rescan reproducibility when measuring AVC volume, density, and Agatston units and is therefore a dependable modality to measure AVC progression, which is the primary outcome of this trial. Whilst women likely will have less calcification at baseline and progress at a slower rate than men, the randomization is likely to ensure equal distribution of sex across treatment groups.^49^

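### The primary model uses baseline AVC as both response and covariate and lists no covariate × time term; read that way, it does not adjust the treatment effect and can understate its standard error

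*Protocol article*

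**What the plan says.** The section Statistical considerations specifies a repeated-measures general linear model for CT-derived AVC volume. Its fixed effects are treatment group, "duration of follow-up (baseline to final visit), and their interaction (treatment × duration of follow-up), with subject as a random effect". The treatment × time "interaction will estimate and test the between-group difference in mean AVC change", so that single coefficient is the primary result. On covariates it says: "Baseline covariates (e.g. age, sex, baseline AVC score) will be included to adjust for potential confounders". The Discussion adds two more, for the limitation of varying vitamin K status: "Baseline ucOC/tOC and estimated dietary vitamin K1 intake will be included as covariates in the repeated measures general linear model". Neither place says whether covariates are crossed with time.

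There are two CT scans per participant. Table 2 marks the scan at the baseline and final visits only, and under Follow-up and trial termination, at the last visit, "all participants will have a repeat clinical assessment and investigations which were performed at baseline". Baseline AVC is therefore one of the two response values in the model.

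Study outcomes defines the primary outcome differently in form: one annualized change in AVC volume per participant. Background and rationale states that "the degree of aortic valve calcification (AVC) in patients with mild or moderate CAS is a key predictor of disease progression".

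**The concern.** A covariate that is constant within a participant and enters only as a main effect shifts both visits by the same amount. It drops out of the change, and the treatment × time coefficient concerns nothing but the change. The stated purpose of the covariates, including the remedy for varying vitamin K status in the Discussion, would then not be achieved for the estimate that matters.

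Baseline AVC raises a second problem, because it is also a response. Conditioning on it removes most of the between-participant variation that the random subject effect is there to absorb. The fitted model can then pool a variance that is too small for the unadjusted estimate it reports. At stake are the nominal 5% level of the only primary test and the precision that baseline AVC could have supplied.

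**Working it through.** **Inputs from the article.** 54 per arm, 1:1; difference 103 μL (181 against 78 μL), from an open-label trial reporting "lower AVC progression in 38 subjects who received vitamin K1 (2 mg per day) for 12 months"; "assuming a common standard deviation of 165" μL; 5% level, taken as two-sided because that reproduces the stated power; follow-up 12 to 21 months, mean 16.

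**Assumed.** The correlation r between baseline AVC and change is not given, so 0 to 0.7 is shown.

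**Step 1: the plan's own figure.** SE = 165 × √(2/54) = 31.75 μL. 103/31.75 = 3.244. Power = Φ(3.244 − 1.960) = Φ(1.284) = 90.0%. The stated 90% is reproduced.

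**Step 2: the estimate.** Write B for baseline AVC and D for change, so the responses are B and B + D. With two coded visits and complete data, the model separates into the sum (2B + D)/√2 and the difference D/√2. Treatment × time appears only in the difference, and subject-constant main effects appear only in the sum. The estimate is therefore mean D on active minus mean D on placebo, whatever main-effect covariates are added. In simulated trials the two agreed to about 1e-12.

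**Step 3: the standard error.** Let σ² = Var(D).
- Difference part: residual variance σ²/2, unadjusted.
- Sum part, given B: residual variance σ²(1 − r²)/2.
- A random intercept with non-negative variance needs the sum part to be at least as variable as the difference part. For r ≠ 0 it is less variable, so the intercept variance goes to zero and the two parts are pooled: [σ²/2 + σ²(1 − r²)/2]/2 = σ²(2 − r²)/4.
- Model SE / true SE = √[(2 − r²)/2]. Type I error = 2[1 − Φ(1.96 × ratio)].

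At r = 0.5: √(1.75/2) = 0.935, and 2[1 − Φ(1.833)] = 6.7%.

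REML fits of the stated model, 54 per arm, no treatment effect:

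| r | SE ratio, formula | SE ratio, simulated | Type I error, formula | 3,000 trials | 20,000 trials |
|---|---|---|---|---|---|
| 0 | 1.000 | 1.000 | 5.0% | 4.6% | 5.0% |
| 0.3 | 0.977 | 0.975 | 5.5% | 5.2% | 5.4% |
| 0.5 | 0.935 | 0.923 | 6.7% | 6.6% | 6.4% |
| 0.7 | 0.869 | 0.883 | 8.9% | 8.0% | 9.0% |

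The last column is a separate simulation. In the 3,000-trial runs the intercept variance was zero in 97% of trials at r = 0.3 and in all at 0.5 and 0.7. A skewed baseline shaped on Table 3 gave 6.5% at r = 0.5.

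**Step 4: what cures it (r = 0.5, 3,000 trials).** With baseline AVC crossed with time: mean SE 27.5 against empirical SD 27.6, type I error 5.4%. With baseline AVC as a response only: SE 31.7 against 31.2, type I error 4.9%.

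**Step 5: power of ANCOVA for 103 μL.** Residual SD = 165√(1 − r²).
- r = 0.3: SD 157.4, SE 30.29, Φ(3.400 − 1.960) = 92.5%.
- r = 0.5: SD 142.9, SE 27.50, Φ(3.745 − 1.960) = 96.3%.

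**Step 6: time in years instead of coded visits.** With individual follow-up of 12 to 21 months, simulated type I error was 6.7%, 7.5%, 8.3% and 9.4% at r = 0, 0.3, 0.5 and 0.7 (1,500 trials each). Part of this comes from unequal follow-up itself: without the baseline covariate it was 5.9% at r = 0.5.

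**The case against.** The strongest reply is that the article never says the covariates are main effects. It calls the model a repeated-measures general linear model, and the multivariate form of that model gives each covariate its own coefficient at each visit, which amounts to covariate × time. In that form the treatment × time estimate equals ANCOVA of change on baseline, and simulated type I error is 4.8–5.1% for r from 0 to 0.7. Terms of this kind, and the covariance structure, are also often left to a SAP. This stands as far as it goes. A reader might infer that the planned adjustment certainly fails, but the text does not establish that. Against it, a random subject effect, listed fixed effects and a single named interaction fit a mixed model better, and the two readings give different primary estimates and standard errors.

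A reader might also infer that the article itself says baseline AVC predicts change in AVC volume. It speaks of disease progression, without tying that to μL of calcium, and gives no correlation. It also allows transformation, so the correlation on the scale finally analysed is unknown. At r = 0.3 or below the excess error is half a percentage point or less with coded visits.

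Nor is the treatment estimate biased. Blinded 1:1 randomization leaves the raw difference in change unbiased, and the Discussion separately plans exploratory analyses by baseline vitamin K status.

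Finally, exact cancellation needs complete data at coded visits. With varying durations, or with missing final scans (four participants had left by March 2025), the estimate shifts somewhat. That shift is still not adjustment of the change for the covariates.

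**Conclusion.** The point holds as a should-fix. The article's wording allows a valid and an invalid version of its primary analysis, and the more natural reading is the invalid one. On that reading (random subject intercept with variance bounded at zero, covariates not crossed with time, complete data at two coded visits) the treatment × time estimate is the unadjusted difference in change. Its test runs at about 5% for r = 0, 5.2–5.5% for 0.3, 6.5% for 0.5 and 8–9% for 0.7.

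The lack of adjustment needs no assumption about r. The excess type I error does, and only baseline AVC causes it: age, sex and vitamin K status as main effects leave the estimate unadjusted but do not distort its standard error. The documents support neither a claim of bias nor a claim that the primary p-value is certain to be anti-conservative. An unstructured covariance would also remove the standard-error problem.

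**What to change.** Make the primary analysis an ANCOVA with one value per participant: annualized AVC volume change, as defined under Study outcomes, on treatment, baseline AVC volume, CAS-severity stratum and the covariates already planned (age, sex, baseline ucOC/tOC, estimated dietary vitamin K1). This matches the primary outcome as defined and uses the stratification factor.

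If the repeated-measures form is preferred, keep AVC at baseline as a response only, constrain the arms to a common baseline mean, use an unstructured covariance, and enter every covariate with a covariate × time term. If crossing with time was always intended, say so.

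The cost is a sentence in the protocol or SAP and one model statement, fixed before unblinding. No new data are needed. The return is a test at its nominal 5% level and, at 54 per arm for the 57% design effect, power of about 92% at r = 0.3 or 96% at r = 0.5 instead of 90%. If r is zero, this power is unchanged at 90%.

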### Blinding and randomization

Eligible patients who provide informed consent to participate in the study will be randomized to receive vitamin K1 or matching placebo. The randomization schedule will be generated using a 1:1 allocation ratio and random block sizes of two or four to either active treatment or placebo. The randomization will be stratified by CAS severity (either mild or moderate) as determined by the peak flow velocity measured on transthoracic echocardiography, to ensure that the treatment and placebo arm have an equal distribution of participants with mild and moderate CAS. The randomization allocation for each participant will be performed by the Royal Perth Hospital clinical trials pharmacy. Participants, referring physicians, trial researchers, and study personnel assessing outcomes will be blinded to treatment allocation.

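### The stated 70% power for a 40% difference does not follow from the plan's own inputs, which give about 62%; the other three stated powers reproduce

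*Protocol article*

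**What the plan says.** All the relevant text is in the protocol article, under Statistical considerations, unless noted.

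- Sample size: the trial, "which will have 54 subjects per study arm (total 108"), is fixed at that number. Under Blinding and randomization: "The randomization schedule will be generated using a 1:1 allocation ratio".
- Primary power claim: the trial "will provide 90% power to detect a 57% difference in AVC progression", with means given as "181 μL in controls vs. 78 μL for active treatment" and "assuming a common standard deviation of 165" μL.
- Further power claims: "This sample size will also provide 80% power to detect a 49% difference and 70% power to detect a 40% difference". The test level for these claims is worded as "at a significance level of 5"%. The text does not say whether the test is one-sided or two-sided.
- Attrition: "We anticipate a low dropout rate of" 5–10%. The paragraph then gives a harsher case, a 25% loss leaving 41 per arm, and states 80% power for the 57% difference in that case.

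**The concern.** The paragraph gives four powers and every input needed to check them. Three fit one simple calculation and one does not. On the printed figures, a true 40% reduction in progression would be missed 30% of the time; on the plan's inputs it would be missed about 38% of the time.

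The 40% case is the smallest effect for which the article states a power. A reader who wants to know how well the trial can see an effect smaller than the one in the earlier open-label study would look at this figure, and it is too favourable. Nothing in the design or analysis depends on it.

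**Working it through.** **Inputs** (Statistical considerations): n = 54 per arm, 1:1; control mean 181 μL; active mean 78 μL; SD 165 μL in both arms; 5% significance, taken as two-sided because that is what reproduces the other figures (shown below).

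**Formula** (normal approximation, two-sided): power = Φ(Δ / SE − 1.96), with SE = SD × √(2/n). I repeated each case with the two-sample t test (noncentral t, 106 degrees of freedom at 54 per arm).

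SE at 54 per arm = 165 × √(2/54) = 31.75 μL. SE at 41 per arm = 165 × √(2/41) = 36.44 μL.

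**Step 1: reproduce the figures that fit.**

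- 57%: Δ = 181 − 78 = 103 μL (103/181 = 56.9%). 103/31.75 = 3.24; 3.24 − 1.96 = 1.28; power 90.0% (t: 89.5%). Stated 90%.
- 49%: Δ = 0.49 × 181 = 88.7 μL. 88.7/31.75 = 2.79; 2.79 − 1.96 = 0.83; power 79.8% (t: 79.0%). Stated 80%.
- 57% with 41 per arm: 103/36.44 = 2.83; 2.83 − 1.96 = 0.87; power 80.7% (t: 79.7%). Stated 80%.

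**Step 2: the figure in question.**

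- 40%: Δ = 0.40 × 181 = 72.4 μL. 72.4/31.75 = 2.28; 2.28 − 1.96 = 0.32; power **62.6%** (t: **61.8%**). Stated 70%.

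**Step 3: look for a reading that rescues 70%.**

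| Alternative | 57% difference | 49% difference | 40% difference |
|---|---|---|---|
| Stated | 90% | 80% | 70% |
| Two-sided 5%, SD 165 (t) | 89.5% | 79.0% | 61.8% |
| One-sided 5%, SD 165 (t) | 94.3% | 87.1% | 73.3% |
| Two-sided 5%, SD 151 (normal) | 94% | 86% | 70% |

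The SD of about 151 μL in the last row is what 70% power at 72.4 μL would require: 72.4 / [(1.960 + 0.524) × √(2/54)] = 151.4. Either alternative breaks the two figures that now fit, and a one-sided test still misses 70%.

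**Step 4: what 70% power does correspond to.**

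- Difference at 54 per arm: (1.960 + 0.524) × 31.75 = 78.9 μL, or 43.6% of 181. By the t test it is 79.6 μL, or 44.0%.
- Sample size for a 40% difference: 2 × (2.484)² × 165² / 72.4² = 64.1, so 65 per arm (about 66 by the t test).

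**Step 5: size of the attrition effect, for context.** A 5–10% loss leaves 54 × 0.95 = 51.3 to 54 × 0.90 = 48.6, so about 51 to 49 per arm.

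| Per arm | 57% difference, normal (t) | 40% difference, normal (t) |
|---|---|---|
| 54 | 90.0% (89.5%) | 62.6% (61.8%) |
| 51 | 88.3% (87.7%) | 60.1% (59.3%) |
| 49 | 87.1% (86.4%) | 58.4% (57.5%) |

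**The case against.** **The planned model adjusts for covariates, which could raise power.** It could. But the power paragraph states no correlation, and the other three figures fit an unadjusted comparison. Any gain would lift all four figures, so it cannot explain one of them.

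**The error is in a secondary statement.** This stands. The sample size rests on the 57% effect, and that calculation is right. Recruitment closed on 1 July 2024 with all 108 randomized (Study status), and a null result would be read mainly from the estimate and its confidence interval. A reader might infer that the trial is underpowered for its stated target, or that its case for detecting smaller effects rests on the 40% scenario. The document supports neither: the primary figure reproduces, and the 49% scenario, also smaller than 57%, is correctly stated.

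**Attrition.** A reader might also infer that the 90% is wrong because 54 per arm is every randomized participant while 5–10% loss is expected. The numbers in Step 5 are true, but this is not an error. The paragraph ties 90% to 54 per arm, discloses the expected loss in the next sentences, and gives a correct power for a much larger loss. It never claims 90% after dropout. Study status reports 4 of 108 lost (3.7%) as of 6 March 2025; if those losses were even between arms, which is an assumption, 52 per arm gives 88.4% by the t test.

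**Rounding.** The t test gives 79.0% for the 49% case, which might tempt one to amend that figure too. The normal approximation gives 79.8%, so 80% is ordinary rounding and should stay.

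**Conclusion.** The pairing of 70% power with a 40% difference is wrong. On the plan's inputs the power is about 62%, roughly 8 points lower, and the chance of missing such an effect is about 38% rather than 30%. The result assumes a two-sided 5% test and an unadjusted two-group comparison, both supported by the three figures that reproduce.

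Whether the slip lies in the power or in the percentage cannot be settled from the document. Printing 40 for 44 would explain it, but that is a guess.

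The importance is low to moderate: a stated property that the design does not have, in a secondary clause, beside a correct primary calculation.

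**What to change.** Change the one clause, in either of two ways: about 62% power to detect a 40% difference, or 70% power to detect a 44% difference (about 79.6 μL). Leave the 90%/57%, 80%/49% and 25%-loss figures as they are. It would help to say that the 5% level is two-sided.

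Optionally, as a clarification and not a correction, add that 90% refers to complete data and that the expected 5–10% loss gives about 88% to 86–87% power for the 57% effect, and about 59% to 58% for the 40% effect (t test).

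The cost is one reworded sentence and a less favourable stated figure. The sample size, endpoint and analysis do not change, and the correction needs no trial data.
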